## Methods

### Design

The design is a prospective study using a convenience sampling method. The novelty of this study is grounded in the approach of a post-operative weighed food diary. Rather than participant recall, ward staff recall or asking ward staff to weigh food (which was not feasible due to ward staff workload), the researcher will weigh and record the participants dietary intake which will therefore increase the accuracy of the data obtained.

Using this design and methodological approach may offset potential refusal to participate in the study as there is no foreseeable risks to the participant nor burden which could potentially lower attrition risks. The design of this study is aimed at exploring biopsychosocial factors associated with older adult hip fracture patients’ outcomes in relation to LOS and post-operative complications. In particular, the inclusion of participants that lack capacity and/or in the presence of comorbidity could provide crucial insight to a subgroup of an at-risk population that has been previously excluded. The study will be conducted in one phase of 4 weeks. Participants enrolled on the study will not be able to obtain their data after the study has been completed as they will be anonymised and assigned a unique reference number after LOS and discharge destination data has been obtained. With no second phase of the study, participants’ identifiable data will not be retained for future research purposes.

### Study sample

The study aims to recruit 30 older adult hip fracture patients admitted to an orthopaedic trauma ward for surgical repair of a hip fracture. A district general sized hospital was chosen as opposed to the scale of a trauma/transplant centre hospital to confer greater generalisability to the population in England with the findings from this study. A sample size of 30 was agreed by the research team based on the admissions data published by the NHFD for the specific study site and is reflective of a ‘typical’ average month of admissions to the hospital, according to 2021 and 2022 data. The decision to enrol 30 patients was primarily based on funding constraints, as there are currently no available funds to support a larger sample. This number was chosen to ensure we can gather detailed and meaningful data while adhering to our timeline and resources. The recruitment period will last for a continuous period of 4 weeks, and all eligible patients according to the inclusion and exclusion criteria will be invited into the study via the gatekeeper as they are admitted to the hospital ward. The standard diagnosis for a hip fracture is an x-ray on admission to the accident and emergency department, following which, the participant's care adheres to a specific ‘neck of femur (NOF) fracture pathway’ which is already in place at the study site.

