### Exclusion criteria

The exclusion criteria for this study are (a) pathological hip fractures, (b) traumatic hip fractures, for example sustained in a road traffic collision, (c) those that cannot speak English language due to obtaining informed consent and (d) those who are undergoing current oncologic treatment.

Due to the design of the study being observational, there are no further exclusions based on medical comorbidity, such as cardiovascular disease, diabetes and renal insufficiency. Those who present with cognitive decline will be approached for inclusion in the study via discussion between medical staff in consultation with a family member/friend whereby following an introduction of the study, their opinion will be sought as to whether they believe their family member or friend that has sustained a hip fracture would be likely to consent to taking part in the study if they had capacity.

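### The target of 30 is set at about one month's hip fracture admissions, but recruitment lasts 4 weeks and only eligible, consenting patients can enrol, so 30 is unlikely to be reached

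*Protocol article*

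**What the plan says.** The relevant text is in the Study sample section of the protocol article.

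- **Target:** "The study aims to recruit 30 older adult hip fracture patients admitted to an orthopaedic trauma ward".
- **Reasons given:** "A sample size of 30 was agreed by the research team based on the admissions data published by the NHFD" for the site, the number being described as reflective of a typical "average month of admissions to the hospital, according to 2021 and 2022 data". The section adds that "The decision to enrol 30 patients was primarily based on funding constraints". No power or precision calculation is offered.
- **Window:** "The recruitment period will last for a continuous period of 4 weeks". No extension is stated, nor any rule to continue until the target is met. The Design section says of the whole study: "The study will be conducted in one phase of 4 weeks".
- **Who can enrol:** patients aged 60 or over whose fracture followed a fall from standing height or less (Inclusion criteria). Four groups are excluded (Exclusion criteria): pathological fractures, traumatic fractures, people who cannot speak English, and "those who are undergoing current oncologic treatment". The ward coordinators act as gatekeepers (Screening). Written consent follows, or, for those lacking capacity, a consultee form after a relative or friend has been asked for an opinion (Enrolment procedure; Ethics and dissemination).

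The article gives no expected eligible share, no consent rate and no allowance for losses.

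**The concern.** The only feasibility support for 30 is a count of admissions over a month. Recruits are a subset of admissions, and 4 weeks is a little shorter than an average month. Each screening and consent step can lower the yield and none can raise it. The target is thus placed at about the level of the whole inflow, with nothing set aside for patients who are ineligible, who decline, or for whom no consultee agreement is obtained.

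Readers will take 30 as the number on which the analyses will rest. These include the average proportion of resting energy expenditure (REE) met and a multiple regression for length of stay that takes in complications, medical history and capacity (Data storage and analysis). That regression is already thin at 30 patients and becomes thinner with every patient short.

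**Working it through.** **Inputs from the document**

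- Target: 30 (Study sample).
- Admissions: about 30 per average month (Study sample). The exact count is not given, so 30 is a reading of the text.
- Window: 4 weeks, or 28 days (Study sample).

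**Assumptions, not in the document**

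- Average month: 365.25 / 12 = 30.44 days.
- Fraction f of admissions that are eligible and enrol: shown from 50% to 100%.
- Enrolments in the window follow a Poisson distribution.

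**Step 1. Can the plan's 30 be reproduced?**

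Expected admissions in the window = 30 × 28 / (days in the month).

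- Average month: 30 × 28 / 30.44 = 27.6
- 30-day month: 30 × 28 / 30 = 28.0
- 31-day month: 30 × 28 / 31 = 27.1
- Month treated as exactly 4 weeks: 30

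The figure of 30 returns only if a month is equated with 4 weeks and every admission enrols. The calendar effect alone is small: 30 − 27.6 = 2.4 patients.

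**Step 2. Expected enrolment and the chance of 30**

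Expected N = 27.6 × f. The chance is P(X ≥ 30) for a Poisson variable with that mean. Weeks needed to expect 30 = 30 / (30 / 30.44 × 7 × f).

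| Assumed f | Expected N in 28 days | P(at least 30) | Weeks needed to expect 30 |
|---|---|---|---|
| 100% | 27.6 | 35% | 4.3 |
| 90% | 24.8 | 17% | 4.8 |
| 80% | 22.1 | 6% | 5.4 |
| 70% | 19.3 | 1.5% | 6.2 |
| 60% | 16.6 | under 0.5% | 7.2 |
| 50% | 13.8 | under 0.5% | 8.7 |

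**Step 3. Does the result hang on the month-versus-4-weeks difference?**

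Take 4 weeks as a full month, with mean 30 × f. The chance of at least 30 is then 52% at f = 100%, 31% at 90% (mean 27) and 13% at 80% (mean 24). The conclusion stands without the calendar effect once any realistic loss is allowed. The unstated fraction f drives most of the shortfall.

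**Step 4. Duration**

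Recruitment takes a continuous 4 weeks, and the Design section gives the whole study 4 weeks. The diary runs from the day of surgery to post-operative day three (Food diary protocol), and participation ends when length of stay and discharge destination are obtained (Adverse events). A patient operated on at day 28 has a diary ending on day 31 and a discharge that may be later still. Both 4-week statements cannot hold literally if patients are enrolled to the end of the window.

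**The case against.** The strongest reply is that the wording is softer than the arithmetic. The article says 30 reflects a typical month. It does not say that 30 is the exact count of all admissions, or whether the count was rounded or already limited to the target population. If the true inflow were higher, or the 30 were already eligible patients, the gap would shrink. That stands, and it is why every figure above is conditional on about 30 admissions a month. As written, though, the text speaks of admissions, and even a month of 30 eligible patients would leave refusal and the shorter window unallowed for.

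Second, the design favours high uptake: little burden, no exclusion for comorbidity and inclusion of people without capacity (Design; Exclusion criteria). This is fair, and it argues against assuming low uptake. At 90% to 100%, however, the expectation is about 25 to 28, still under 30.

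Third, funding is named as the primary reason for 30. Funding explains why the number cannot be larger; it does not make 30 attainable in 4 weeks.

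Fourth, the article already urges caution over the small sample (Data storage and analysis; Strengths and limitations). Those caveats concern a sample that is small, not one that falls short of its stated size.

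Finally, the article only aims at 30, and detailed accrual forecasts may sit in the full protocol. Their absence is not the complaint. The complaint is that the reason given for 30 and the window, set out in the same section, do not fit together.

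**Conclusion.** The point holds as a mismatch between the target and the recruitment window. On about 30 admissions a month, 28 days bring about 27.6 before any exclusion or refusal. The chance of reaching 30 is about 35% at full uptake, 17% at 90%, 6% at 80% and 1.5% at 70%. With an assumed uptake of 50% to 100%, the expected size is about 14 to 28. These figures rest on the reading of the monthly count, on the Poisson model and, above all, on an uptake that the document does not give.

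A reader might go further and conclude that the study will deliver only about 14 to 22 patients. The document does not support that: it would need an uptake of about 51% to 80% (14 / 27.6 and 22 / 27.6), which appears nowhere.

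A reader might also try to express the loss as a wider confidence interval in kcal, using the SD of 354 kcal/day quoted in the Introduction. That SD comes from lunch and dinner without fluids in 15 patients. This study records all food, fluid and supplements and bases its inference on the proportion of REE met, so the SD does not measure the precision of its primary estimate.

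**What to change.** In the Study sample section, do one of the following:

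1. Keep the 4 weeks. Call 30 the funded maximum and state the number expected from the window, with the monthly admissions and assumed uptake shown. Until a site-specific uptake is available, this would read as about 14 to 28 expected for 50% to 100% uptake.
2. Keep 30. If funding and timeline allow, define recruitment as continuing until 30 are enrolled. On the same assumptions, 30 would be expected after about 4.3 weeks at full uptake, 5.4 at 80% and 8.7 at 50%.

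In either case, reconcile the one-phase duration in the Design section with the diary and length-of-stay follow-up. For example, state that the 4 weeks refer to recruitment and that follow-up runs until the last participant's discharge data are obtained.

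The first option costs wording only, and its downside is a less favourable stated size. The second costs time and researcher effort, which the stated funding limits may not permit.

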### Inclusion criteria

The inclusion criteria for this study are adults aged 60 years and above that have sustained a hip fracture from a fall at standing height or less. There is no upper age limit, and no exclusions based on gender or ethnicity.

### Exclusion criteria

The exclusion criteria for this study are (a) pathological hip fractures, (b) traumatic hip fractures, for example sustained in a road traffic collision, (c) those that cannot speak English language due to obtaining informed consent and (d) those who are undergoing current oncologic treatment.

Due to the design of the study being observational, there are no further exclusions based on medical comorbidity, such as cardiovascular disease, diabetes and renal insufficiency. Those who present with cognitive decline will be approached for inclusion in the study via discussion between medical staff in consultation with a family member/friend whereby following an introduction of the study, their opinion will be sought as to whether they believe their family member or friend that has sustained a hip fracture would be likely to consent to taking part in the study if they had capacity.

### Screening

Each day, the researcher (HL) will check with the trauma coordinators on the ward responsible for the triage of hip fracture patients regarding new hip fracture admissions and discuss the potential for the participant to be approached for the study. On admission to the ward, the coordinators responsible for the admission and preparation of the hip fracture patient for surgery (the gatekeepers) will ask the participant if the researcher can be introduced to discuss the study.

### Enrolment procedure

With agreement, the researcher will discuss the study with the participant and family or carers if present and provide the participant with a patient information sheet (PIS) and consent form to read in full. After 1 hour, the researcher will return and obtain informed consent. The lead researcher for this study is a current registered healthcare professional with the Health and Care Professions Council in the UK and has training and experience of obtaining written informed consent. With the participants consent, the researcher, working with the specialist nurse will obtain data from the participant's medical records pertaining to outcome measures (Table 1).

**Table 1. table1-02601060241307768:** Outcome measures.

Variable	Instrument/scale
Age	Age will be measured in years based on the date of birth obtained from medical records.
Sex	As recorded in medical records.
Ethnicity	As recorded in medical records.
Original domicile	Defined as own home/care home/sheltered accommodation, according to medical records.
Mobility status prior to admission	Defined as independent/independent with 1 stick/independent with 2 sticks/independent with frame/wheelchair.
Nutritional screening	Screening assessment according to the Malnutrition Universal Screening Tool (0, 1 or 2).
BMI	Calculated by ward staff; where not possible, MUAC score.
REE	Calculated according to guidance (Todorovic and Mafrici, 2018)
Smoking status	Confirmed on admission; answered as yes or no.
Alcohol	Confirmed on admission; calculated as units per week.
Fracture type	Classified as intra-capsular or extra-capsular, confirmed on admission with an x-ray performed in the emergency department.
ASA Grade	Classified following anaesthetic pre-assessment by anaesthetist (1–5).
Acute length of stay	Measured from admission to discharge from the acute ward, in days.
Discharge location	Defined as original domicile/rehabilitation unit/care home.
Past medical history	Data will be obtained from medical records regarding cardiovascular, respiratory, diabetes, cognitive decline, arthritis and history of previous fractures.

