## Introduction

Older adult hip fracture patients are a significant surgical population in England, with over 65,000 cases registered in 2022 according to the National Hip Fracture Database (NHFD) (2023a) with average 30-day mortality rates at just over 6% (NHFD, 2023b). Approaches to in-patient care has seen marked developments in recent years, including orthogeriatric assessment, surgery within 36 hours of diagnosis and early mobilisation; strategies that have been incentivised via the Best Practice Tariff (National Health Service (NHS England, 2021) and hospital key performance indicators specified by the NHFD (2023c). However, an aging population and the long-term effects of COVID-19 has increased the risk of frailty (NHFD, 2023c), morbidity and polypharmacy, which can present challenges in providing even basic care needs, including supporting nutrition and dietary intake.

Malnutrition is a modifiable risk factor, and as outlined in an earlier review by Cochrane, malnutrition is prevalent in the hip fracture population (Avenell et al., 2016). However, the review explored supplementation strategies rather than dietary intake since patients ‘may have poor food intake while in hospital’. Conversely, studies of nutritional status have repeatedly demonstrated a correlation between malnutrition and lower functional outcome (Wong et al., 2021), mortality at 3, 6 and 12 months and the presence of post-operative delirium (Zanetti et al., 2019), however, focus has been on the most appropriate nutritional screening tool as opposed to opportunities for dietary improvement.

Current guidance in relation to specific nutritional support for hip fracture patients is limited, and rather the indication for nutritional support is based on a generic risk assessment for all adults regardless of condition or injury (NICE, 2024). The NHFD has measured nutritional risk assessment compliance since 2016 (NHFD, 2017), with the Malnutrition Universal Screening Tool (MUST) most used and is currently validated by both the British Association for Parenteral and Enteral Nutrition (BAPEN) and the National Institute for Health and Care Excellence (NICE) (BAPEN, 2003; NICE, 2024).

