### Research aims

The primary aim is to observe if the post-operative dietary energy intake (kJ/kcal) of older adult hip fracture patients meets their REE needs that would allow for basic movements, such as from bed to chair and initial mobilisation with a physiotherapist post-surgery.

Secondly, the aims of the study are to explore if there is a correlation between post-operative dietary intake and LOS; to explore the relationship between comorbidity (where reported) and post-operative dietary intake, according to dietary intake; and to explore (if) in the development of post-operative complications (including, delirium, infection, pressure ulcers and venous thromboembolism), there is a correlation with post-operative dietary intake.

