### Food diary protocol

The weighed food diary will commence on the participants day of surgery (day zero) and will conclude at post-operative day three inclusive. The weighed food diary will consist of the researcher using an electronic digital kitchen scale with a weight graduation of 1 g (AccuWeight 201, maximum weight 5 kg) to weigh all items served to the participant before and after their mealtime. The researcher will not serve any food directly, with plates or bowls placed directly on the digital scale and recorded by the researcher. Should a food be packaged with a specified weight – for example a yoghurt, said weight on the packaging will be recorded. Fluid intake will be recorded according to each mealtime (e.g. a cup of tea or fruit juice) and the researcher will liaise with the ward staff to log how many jugs of water the participant has consumed daily, and if this has been accompanied with other items such as cordial. A baseline measurement of water jugs, cups and beakers will be taken prior to the study commencing.

The researcher will not be present nor disrupt the participant during their meal, and after their food tray has been retrieved, the researcher will weigh the plate if it is a complete meal (e.g. lasagne), or, if it is a multiple item meal (e.g. meat, potatoes and vegetables), the researcher will weigh the leftover components individually to ensure the validity of the weighed food method and to achieve the highest degree of accuracy possible. After mealtime has concluded, the researcher will briefly ask the participant if they have had any snacks between their meals. Any observed assistance with meals (such as a family member) will be confirmed with ward staff. Additionally, as part of the specific NOF pathway in place, all hip fracture patients regardless of MUST screening assessment are required to consume two oral nutritional supplements (Nutricia™ Fortisip Compact or Fortisip Compact Protein) daily. The researcher will liaise with the ward staff regarding consumption and additionally will record the amount consumed. Data will also be collected regarding the times of meals and the ratio of staff to patients on the ward during each mealtime.

The researcher will liaise daily with the participant's named nurse regarding complications that may develop post-operatively during the study period, such as delirium, pressure ulcers, infection and venous thromboembolism.

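### In the secondary intake–LOS analysis, the stay is counted from admission rather than surgery, and a death on the ward has no valid LOS or discharge destination

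*Protocol article*

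**What the plan says.** One secondary aim is to "explore if there is a correlation between post-operative dietary intake and LOS" (Research aims). Table 1, under Enrolment procedure, fixes the outcome: acute LOS is "Measured from admission to discharge from the acute ward, in days". The exposure has a later start: "The weighed food diary will commence on the participants day of surgery (day zero) and will conclude at post-operative day three inclusive" (Food diary protocol).

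Data storage and analysis plans a multiple regression with LOS as the dependent variable and REE as the predictor, read here as the share of REE met, averaged over the diary. The named confounders are complications, medical history and capacity. Time from admission to surgery is not among them and is not a Table 1 variable.

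Discharge location in Table 1 is "Defined as original domicile/rehabilitation unit/care home". All three are destinations of living patients. Under Adverse events, a participant's end point is reached once LOS and discharge destination are known. Participants with events such as stroke or myocardial infarction are removed, and their data up to removal are kept; death is not named.

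The Introduction cites "with average 30-day mortality rates at just over 6" per cent. The criteria set no upper age limit and admit patients with comorbidity and cognitive decline.

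**The concern.** There are two separate problems, both in definitions that the article states in full.

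**Start of the clock.** Days before surgery precede the exposure, so intake cannot have caused them, yet they count in the outcome. If the wait is unrelated to intake, this is only noise. If sicker patients both wait longer and eat less, it produces a negative intake–LOS slope (lower intake, longer stay) even when intake has no effect. That is the direction the Hypothesis section expects.

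**Deaths.** The outcome ends at discharge, and the destinations form a closed list without death. A ward death therefore has no value for either variable and does not reach the defined end point. Whoever builds the dataset must improvise. Entering time to death as LOS scores an early death as a short stay, in an analysis where a longer stay is the bad result. Leaving the patient out loses the worst outcome. With 30 patients, one or two such choices can move the slope.

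**Working it through.** The sample size of 30 rests on funding and a typical month of admissions (Study sample). There is no power calculation to reproduce.

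**1. How likely is a death?** Inputs: n = 30 (Study sample); mortality p = 6%, for just over 6% (Introduction). Expected deaths = n × p; P(at least one) = 1 − (1 − p)^30.

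| p | Status | Expected deaths | P(at least one) |
|---|---|---|---|
| 6% | cited, national, 30-day | 1.8 | 84% |
| 4% | assumed acute-ward share | 1.2 | 71% |
| 3% | assumed | 0.9 | 60% |
| 2% | assumed | 0.6 | 45% |

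The 6% row includes deaths after leaving the acute ward, which do not affect this LOS. The documents do not give the acute-ward share, so the lower rows are a range, not an estimate.

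**2. What does the wait do?** The assumptions for steps 2 and 3 are not in the documents: post-operative LOS with mean 12 and SD 6 days and a floor of 4; pre-operative wait with mean 1.5 days and SD 1, not below zero. The mean matches the Introduction's 36-hour strategy (36/24 = 1.5), which is not site data. Each setting was simulated 5,000 times with n = 30, regressing LOS on standardised intake with no true effect.

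| Correlation of wait with intake | Slope, LOS from surgery | Slope, LOS from admission |
|---|---|---|
| 0 | 0.0 | 0.0 |
| -0.3 | 0.0 | -0.27 |
| -0.5 | 0.0 | -0.46 |

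Slopes are days per SD of intake. A hand check agrees: correlation × SD of wait gives -0.3 × 1 = -0.30 and -0.5 × 1 = -0.50, slightly reduced because the wait cannot be negative. The noise is small: the variance rises from about 36 to 36 + 1 = 37, and √(37/36) ≈ 1.014, so the standard error grows by roughly 1.4%. The standard error of the slope is about 1.1 days.

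**3. What does the handling of deaths do?** Further assumptions: an association of nominally -2 days per SD (about -1.79 after the 4-day floor); deaths more likely at low intake (log-odds of 1 per SD); a death, if entered as a stay, recorded as 5 days.

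| Handling | Death rate | Slope |
|---|---|---|
| No deaths | – | -1.79 |
| Death entered as 5-day stay | 6% | -1.19 |
| Death entered as 5-day stay | 3% | -1.47 |
| Deaths dropped | 6% | -1.77 |

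Entering deaths as stays moves the slope by 1.79 − 1.19 = 0.60 days at 6% and 1.79 − 1.47 = 0.32 days at 3%, or 0.60/1.1 ≈ 0.55 and 0.32/1.1 ≈ 0.29 of a standard error. Dropping deaths hardly moves it. The slope therefore depends on a choice that the article leaves open.

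**The case against.** The strongest reply is that the harm from deaths is inferred. A reader might conclude that the plan scores an early death as a short, favourable stay. It does not say so. On the plain wording a patient who dies is not discharged and so has no LOS, and under that reading the slope barely changes (-1.77 against -1.79). That stands. What remains is that the plain reading is not written as a rule and leaves the end point under Adverse events unreachable. The removal rule there has an open list of events and might take in a fatal one, but it still supplies no LOS or destination.

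A reader might also take 84% as the chance of a death that affects this analysis. It is a 30-day figure and an inappropriate measure of acute-ward deaths.

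On the clock, counting from admission is clear and internally consistent, and it does not bias the slope by itself. Bias needs a link between wait and intake that the documents neither show nor exclude. The planned adjustment for medical history and capacity may absorb part of it. Sicker patients may also stay longer after surgery, so moving the origin does not cure confounding by severity. All of this limits the size of the problem. None of it is a reason to keep days in the outcome that the exposure cannot affect.

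Handling of deaths in a secondary regression could sit in a fuller document. The LOS definition and the closed list of destinations, however, are stated here and need changing here.

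**Conclusion.** The point holds at modest size. The LOS origin does not match the exposure, and a plausible event has no valid value in either LOS or discharge location. Under the stated assumptions, the wait shifts the slope by 0 to -0.46 days per SD of intake. Entering deaths as 5-day stays weakens a true association by about 0.3 to 0.6 days per SD; on average it does not reverse it. Every shift is below the standard error of about 1.1 days. These sizes depend on the assumed LOS distribution, the link between wait and intake, and the tilt of deaths towards low intake. LOS is a secondary, exploratory outcome, and the primary comparison of energy intake with REE is unaffected. The change is worth making because it is nearly free and removes a choice that would otherwise be made after the data are seen.

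**What to change.** 1. For the regression, define LOS as days from surgery (diary day zero) to live discharge from the acute ward. Keep LOS from admission as a descriptive figure.
2. Add time from admission to surgery to Table 1 and use it as a baseline covariate.
3. Add *died in hospital* to discharge location, and let the end point under Adverse events be reached by death as well as by discharge.
4. State that time to death is not entered as LOS. Report deaths separately, with intake, and add one rank-based sensitivity analysis that places deaths as the worst LOS. A full competing-risk model is optional with 30 patients.

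The cost is a few lines in Table 1 and the analysis section, plus one extra model term, which is a small but real demand on 30 observations. The day of surgery must already be known to start the diary, and admission and death dates should be in the medical records. Residual confounding by severity of illness remains and should be acknowledged when the slope is interpreted.
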